## Abstract

**Background:**

Early detection of vital sign changes is key to recognizing patient deterioration promptly, enabling timely interventions and potentially preventing adverse outcomes.

**Objective:**

In this study, vital parameters (heart rate, respiratory rate, oxygen saturation, and blood pressure) will be measured using the Comestai app to confirm the accuracy of photoplethysmography methods compared to standard clinical practice devices, analyzing a large and diverse population. In addition, the app will facilitate big data collection to enhance the algorithm’s performance in measuring hemoglobin, glycated hemoglobin, and total cholesterol.

**Methods:**

A total of 3000 participants will be consecutively enrolled to achieve the objectives of this study. In all patients, personal data, medical condition, and treatment overview will be recorded. The “by face” method for remote photoplethysmography vital sign data collection involves recording participants’ faces using the front camera of a mobile device (iOS or Android) for approximately 1.5 minutes. Simultaneously, vital signs will be continuously collected for about 1.5 minutes using the reference devices alongside data collected via the Comestai app; biochemical results will also be recorded. The accuracy of the app measurements compared to the reference devices and standard tests will be assessed for all parameters. CIs will be calculated using the bootstrap method. The proposed approach’s effectiveness will be evaluated using various quality criteria, including the mean error, SD, mean absolute error, root mean square error, and mean absolute percentage error. The correlation between measurements obtained using the app and reference devices and standard tests will be evaluated using the Pearson correlation coefficient. Agreement between pairs of measurements (app vs reference devices and standard tests) will be represented using Bland-Altman plots. Sensitivity, specificity, positive predictive value, negative predictive value, accuracy, and likelihood ratios will be calculated to determine the ability of the new app to accurately measure vital signs.

**Results:**

Data collection began in June 2024. As of March 25, 2025, we have recruited 1200 participants. The outcomes of the study are expected at the end of 2025. The analysis plan involves verifying and validating the parameters collected from mobile devices via the app, reference devices, and prescheduled blood tests, along with patient demographic data.

**Conclusions:**

Our study will enhance and support the accuracy of data on vital sign detection through PPG, also introducing measurements of biochemical risk indicators. The evaluation of a large population will allow for continuous improvement in the performance and accuracy of artificial intelligence algorithms, reducing errors. Expanding research on mobile health solutions like Comestai can support preventive care by validating their effectiveness as screening tools and guiding future health care technology developments.

**Trial Registration:**

ClinicalTrials.gov NCT06427564; https://clinicaltrials.gov/study/NCT06427564

## Introduction

In recent decades, there has been an increasing focus on self-monitoring apps in primary care, which, with the advent of new technologies, have become more convenient and accessible for patients [1-3].

The use of mobile health (mHealth) apps is undeniably a valuable tool for enabling self-monitoring and health care interventions [4,5]. Specifically, the advancement of noncontact techniques for monitoring human vital signs holds significant potential to enhance patient care across various settings [6,7].

By enabling easier and more convenient monitoring, these techniques can mitigate serious health issues and improve patient outcomes, particularly benefiting individuals who cannot or prefer not to visit traditional health care settings. Vital signs are objective measures of the essential physiological functions of a living organism and they are the critical starting steps in any clinical evaluation.

Early detection of changes in vital signs typically correlates with faster identification of changes in the patient’s health status and the escalation of care if necessary [8]. Alterations in vital signs preceding clinical deterioration are well documented, and the early identification of preventable outcomes is crucial for timely intervention [8]. Logically, the more frequently vital signs are measured, the quicker clinical deterioration can be detected.

The app named Comestai is a noninvasive and easy-to-use tool that enables the measurement of different vital parameters. The app allows users to simultaneously measure vital parameters such as heart rate (HR), respiratory rate (RR), oxygen saturation (SpO_2_), blood pressure (BP), hemoglobin (Hb), and glycated hemoglobin A_1c_ (HbA_1c_) using the photoplethysmographic method with the front camera of a mobile device.

Photoplethysmography is a practical method for noncontact vital sign measurement using a red-green-blue (RGB) camera that has been recently introduced [6,9]. Photoplethysmography uses a transducer that emits infrared light from an LED into the dermis. The adjacent photodetector measures the backscattered light, which is then represented as a line tracing. The intensity of the backscattered light changes with the volume of red blood cells in the dermal capillaries [9]. Photoplethysmography captures color change signals collected from various regions of the face, correlating the estimated magnitudes of red cell aggregation influenced by blood perfusion with the reflected light intensity in each region. By comparing variations in the averaged color signals, the camera-based signal-to-noise ratio estimates are enhanced.

As reported by [10,11], photoplethysmography has shown promising results in measuring vital signs and could be a valuable tool for the early detection and screening of cardiovascular, respiratory, and metabolic conditions. These interventions could be crucial in combating noncommunicable chronic diseases (NCDs) [12]. Furthermore, literature data on the use of photoplethysmography for vital sign detection usually refer to controlled clinical settings. Larger, more diverse populations need to be included to ensure accuracy across various demographics and health conditions [10,12,13].

In this study, vital parameters will be measured using the Comestai app to confirm the accuracy of photoplethysmography methods compared to standard clinical practice devices, analyzing a large and diverse population. In addition, the app will facilitate big data collection to enhance the algorithm's performance in measuring Hb, HbA_1c_, and total cholesterol. The results will be useful to determine whether this user-friendly mobile app achieves adequate accuracy and can be adopted to enhance self-monitoring of health status and detect early health deterioration. A secondary result will be the collection of raw data that can be used to train the algorithm to detect other vitals.

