### Criteria for Data Collection and Study Interruption

Temporal interruption of vital signs data collection using the app may occur in the following cases:

Technical issues with the investigational and/or reference devicesThe study may be interrupted for the following reasons:Breach of participant confidentiality.Decision by the principal investigator or institutional ethics committee.The investigators may also decide to terminate the study early if sufficient data has been collected for algorithm improvement.

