### Statistical Analysis

Numerical variables will be presented as minimum and maximum values, means, SDs, medians, and quartiles. Categorical variables will be presented as absolute and relative frequencies.

The accuracy of the app measurements compared to the reference devices and standard tests will be assessed for all parameters. CIs will be calculated using the bootstrap method. Participants with abnormal adverse events (defined as 3 SDs or more above the mean) and those with invalid reference device values will be excluded from the analysis.

In order to provide a more comprehensive view of the model’s performance, the proposed approach’s effectiveness was evaluated using various quality criteria, including the mean error, SD, mean absolute error, root mean square error, and mean absolute percentage error. The correlation between measurements obtained using the app and those from reference devices and standard tests will be evaluated using the Pearson correlation coefficient. The agreement between the 2 sets of measurements (app vs reference devices/standard tests) will be represented using Bland-Altman plots. Sensitivity, specificity, positive predictive value, negative predictive value, accuracy, and likelihood ratios will be calculated to determine the ability of the new app to accurately measure vital signs.

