## Discussion

### Principal Findings

The project aims to report whether this user-friendly mobile app supports a high level of accuracy in monitoring SpO_2_, RR, BP, and PR, demonstrating the same reliability in detecting Hb, HbA_1c_, and total cholesterol. Enhancing algorithm performance and achieving a high level of accuracy will be crucial in assessing whether the app can be adopted to improve self-monitoring of health status. This, in turn, could enhance the screening for early abnormalities in vital signs and biochemical parameters.

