### Conclusion

Our study will enhance and support the accuracy of data on vital sign detection through PPG, also introducing measurements of biochemical risk indicators. The evaluation of a large population will allow for continuous improvement in the performance and accuracy of AI algorithms, reducing errors. Expanding research opportunities to evaluate mHealth solutions as effective and dependable screening tools is useful for preventive strategies, reducing the burden of NCDs [27]. App solutions, such as Comestai, may present new opportunities and challenges related to technology use in the health care sector, offering insights and guiding future research directions.

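### For Hb, HbA1c and total cholesterol, one cohort both improves the algorithm and is scored for accuracy, with no stated separation; the early-stop clause follows the improvement goal, not the accuracy goal

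*Protocol article*

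**What the plan says.** The Introduction separates the aims by parameter. For vital signs, "vital parameters will be measured using the Comestai app to confirm the accuracy of photoplethysmography methods compared to standard clinical practice devices". For the blood markers, "In addition, the app will facilitate big data collection to enhance the algorithm", and the sentence ends by limiting this to "performance in measuring Hb, HbA_1c_, and total cholesterol". It adds: "A secondary result will be the collection of raw data that can be used to train the algorithm to detect other vitals".

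The Recruitment section assigns a single sample of 3000 to all objectives. Under Statistical Analysis, "The accuracy of the app measurements compared to the reference devices and standard tests will be assessed for all parameters"; the standard tests are the blood tests. Principal Findings seeks equal reliability for the three blood markers and continues: "Enhancing algorithm performance and achieving a high level of accuracy will be crucial in assessing whether the app can be adopted". The Conclusion is general: "The evaluation of a large population will allow for continuous improvement in the performance and accuracy of AI algorithms, reducing errors".

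On ending the study, the section on data collection and study interruption says: "The investigators may also decide to terminate the study early if sufficient data has been collected for algorithm improvement". It gives no number and no accuracy criterion.

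Two statements bear on whether retraining during the study is possible. Data Collection and Management says the app runs offline and the company has no access to the test data. Potential Risks says vital-sign data are kept on the company's own cloud. Under Ethics Approval, sharing blood results is optional.

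**The concern.** Error measured in people whose data tuned a model is apparent error. It understates error in a new user, and a bootstrap interval around the apparent figure does not correct this. The article gives the three blood markers both roles in one cohort: their algorithm is to be improved with these data, and their accuracy is to be reported from these data. They are also what the Discussion presents as the app's added value, because few publications exist on estimating them this way. A reader could take a training-set result for performance in new users.

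The stop clause raises a separate matter. It lets the improvement goal end enrolment, although the power statement rests on 3000 participants and concerns the comparison with reference methods.

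**Working it through.** **1. Which parameters have both roles**

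| Parameters | Improve algorithm on this cohort? | Report accuracy in this cohort? |
|---|---|---|
| Hb, HbA1c, total cholesterol | Yes, stated in Abstract and Introduction | Yes, Statistical Analysis and Principal Findings |
| HR, RR, SpO2, BP | Not stated in Methods; only general prose in the Discussion and conclusions | Yes |
| Other vitals | Possible training use of raw data, as a secondary result | No |

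The overlap is explicit only in the first row.

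**2. The plan's own figure**

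Sample Size Estimation states power above 95% with n = 3000 and two-sided alpha 0.05. This cannot be reproduced, because Table 2 gives upper limits on RMSE and MAE with no SD, mean difference or null value. As one possible reading, take a paired test of mean bias, with d = bias / SD of differences:

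power = Φ(d√n − 1.96) + Φ(−d√n − 1.96)

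- n = 3000: 95% power at d = (1.960 + 1.645)/√3000 = 0.066.
- Same d, n = 1200 (the number recruited by 25 March 2025, used only to illustrate an early stop): d√n = 0.0658 × 34.64 = 2.28, so power is about 63%.

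The stated power is therefore neither confirmed nor refuted, but any such figure depends on reaching the planned n.

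**3. Size of the optimism if the same people tune and score**

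Assumptions, none of them from the article: a least-squares model with p fitted parameters and random Gaussian predictors, relative to the true error SD.

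- Apparent RMSE factor: √(1 − p/n)
- New-user RMSE factor: √(1 + p/(n − p − 1))

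| n | p | Apparent | New users | Ratio |
|---|---|---|---|---|
| 3000 | 10 | 0.998 | 1.002 | 0.997 |
| 3000 | 100 | 0.983 | 1.017 | 0.967 |
| 3000 | 300 | 0.949 | 1.054 | 0.90 |
| 1200 | 10 | 0.996 | 1.004 | 0.992 |
| 1200 | 300 | 0.866 | 1.155 | 0.75 |

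Simulation at n = 3000, p = 300 and error SD 3 gave an apparent RMSE of 2.85 against 3.16 in new data. For scale, a limit of 3 would be met in the first and missed in the second. Table 2 sets no limit for the blood markers, so this only shows how a verdict could flip. With nothing fitted on these participants the ratio is 1. The n = 1200 rows show that the gap widens when fewer people contribute, as optional blood results make likely.

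**4. Precision**

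For normal errors, the relative 95% half-width of RMSE is about 1.96/√(2n): 2.5% at n = 3000, 4.0% at 1200, and 4.6% at 900 (an assumed 30% hold-out of 3000). Stopping on quantity of data costs precision; it does not shift the estimate.

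**The case against.** Collecting data to improve an algorithm is not the same as testing on training data. If the current app is evaluated and the data are kept for a later version, the accuracy estimate is unbiased. Several statements fit that reading: measurement is described as real time and offline, the company is said to have no access, and the training use for other vitals may lie in the future. A version lock or data split could also sit in the full protocol, which is not shown, and a condensed article need not repeat it. The sentences on continuous improvement are discussion prose, not analysis rules.

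Much of this stands. A reader might infer that all 3000 participants both train and validate the whole app. The documents do not support that: the enhancement aim names three blood markers, no Methods text says the vital-sign algorithms are retrained before evaluation, and blood results are optional. A reader might also infer that investigators could stop when results look good. The clause speaks of sufficient data, which is quantity, and mentions no look at accuracy.

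The no-access statement is not decisive, because Potential Risks places vital-sign data on the company's cloud. If the company truly had no access, the stated aim of improving its algorithm would need some other route. Nor does the point rest on silence alone: the article itself gives the blood markers both roles, and the stop clause is explicit.

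**Conclusion.** The point holds in limited form, as a cheap improvement rather than a flaw that undermines the study. For Hb, HbA1c and total cholesterol, the article as written allows accuracy to be reported in participants who shaped the algorithm. If that happens, accuracy would be optimistic. The size cannot be stated, because model complexity is not given: on the assumed least-squares model with n = 3000, the RMSE understatement relative to new users runs from about 0.3% at 10 fitted parameters to 10% at 300. It would be larger with fewer participants. It is zero if the evaluated version was fixed beforehand. It would therefore go too far to say that the accuracy claim is optimistic; the text shows only that it may be.

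For HR, RR, SpO2 and BP, evaluating one locked and recorded version in all participants is enough.

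The stop clause is a separate weakness. It can reduce the 3000 behind the stated power without reference to the accuracy objective. It would bias accuracy only if sufficiency were judged on observed results, which the text does not say.

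**What to change.** 1. Record and lock the app version used for all accuracy analyses.
2. If any biochemical model is tuned on study data, report its accuracy only in participants not used for tuning. Split by participant, for example by enrolment date or site, and withhold the test participants' blood values from developers until the app outputs are fixed.
3. Reword the early-termination clause so that enough training data ends training use only, and enrolment ends on the planned validation count.
4. Reconcile Data Collection and Management with Potential Risks on company access and cloud storage.

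The cost is protocol wording and one data-access rule. Fewer participants remain for biochemical training, and biochemical validation intervals widen by about 1/√f when a fraction f is held out: 1.83 times at f = 0.30 and 1.29 times at f = 0.60 (both fractions assumed). The vital-sign sample need not shrink.

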## Methods

### Recruitment

The objectives of this study will be achieved by recruiting 3000 participants from the outpatient clinic of ASST-Fatebenefratelli-Sacco, Buzzi Children’s Hospital, and IRCCS MultiMedica in Milan, Italy. All participants who meet the inclusion criteria and provide consent to participate will be enrolled consecutively. Recruitment will take place from June 2024 to September 2025.

### Eligibility Criteria

Participants eligible for inclusion in the study must meet the criteria in Textbox 1.

In addition to the above criteria, 70% of the target population should include adult participants meeting at least one of the conditions in Textbox 2. Family history of diabetes or hypertension will also be investigated.

The procedures and evaluations in Textbox 3 will be performed during screening to enroll eligible participants.

Characterizing aspects will be noted, such as scars, piercings, beards, glasses, or the use of facial products, sunscreen cream, or nail polish. Furthermore, current pregnancy will be reported.

The flowchart of the process is schematized in Figure 1.

Inclusion and exclusion criteria.
**Inclusion criteria**
Must demonstrate the ability to comprehend and provide written informed consent.Male or female participants aged ≥16 and ≤65 years.Must be willing and able to adhere to study procedures.
**Exclusion criteria**
Participants will be excluded if they meet any of the following conditions:Compromised circulation, injury, or physical abnormalities affecting fingers, hands, ears, forehead/skull, or other regions of interest essential for study testing.The presence of tattoos in the optical path hinders the assessment of necessary regions of interest.Severe allergies to standard adhesives, latex, or other materials used in medical sensors for measuring vital signs.Medical conditions that, in the investigator’s opinion, prevent the conduct of study assessments.Considered unfit for participation by the investigator.

Additional inclusion criteria.Prediabetes or diabetes with glycated hemoglobin (HbA_1c_) levels between 5.7% and 13%:30% of participants with HbA_1c_ 5.7%-6.4%.30% of participants with HbA_1c_ >6.4%.Hypertension with systolic measurements exceeding 130 mm Hg:40% of participants with systolic blood pressure >130 mm Hg.20% of participants with systolic blood pressure >160 mm Hg.Total cholesterol:40% of participants with levels >200 mg/dL and/or low-density lipoprotein cholesterol >130 mg/dL.Atrial fibrillation (~1% prevalence).Smokers, constituting approximately 20%-30% of the study cohort.

Procedures and evaluations.Obtain participant consent and, if agreed, additional consent for a blood sample.Review eligibility: assess eligibility as described in the inclusion and exclusion criteria.Record the participants’ medical and medication history: each medical problem encountered is classified into the sector of the body involved and for each of these, the starting date and the drugs used for treatment are indicated.Record participant demographics, including date of birth, age, smoking, and alcohol drinking habits.Record body characteristics including height, weight (BMI will be calculated as a person’s weight in kilograms divided by the square of height in meters), and skin tone using the Fitzpatrick scaleInterview the patient about his feelings in the last 2 weeks and if he has suffered from problems such as anxiety, nervousness, lack of control, loss of interest in doing things, or depression.

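### The recruitment quotas load the cohort with systolic pressures above 160 mm Hg, so an unstratified sensitivity or likelihood ratio depends on the quota and tends to overstate detection of moderately raised pressure

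*Protocol article*

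**What the plan says.** Under Eligibility Criteria, the protocol article requires that "70% of the target population should include adult participants meeting at least one of the conditions in Textbox 2". For systolic pressure, Textbox 2 then sets "40% of participants with systolic blood pressure >130 mm Hg" and "20% of participants with systolic blood pressure >160 mm Hg". It does not say whether the second group lies inside the first. It also does not say whether the percentages apply to all 3000 participants or only to the enriched 70%. For HbA1c the same textbox gives one quota for 5.7%-6.4% and another, "30% of participants with HbA_1c_ >6.4", which are separate bands of equal size.

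The Statistical Analysis section says: "Sensitivity, specificity, positive predictive value, negative predictive value, accuracy, and likelihood ratios will be calculated to determine the ability of the new app". It names no cut-off, severity band or weighting for these measures. Under Principal Findings, the hoped-for use is to "enhance the screening for early abnormalities in vital signs and biochemical parameters".

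**The concern.** When a continuous quantity is dichotomised, sensitivity is an average over how far the cases lie beyond the cut-off. Cases 30 mm Hg or more past it are rarely missed, and cases just past it often are. In this cohort the balance between the two is set by a quota and does not arise from the population in which the app would be used. A pooled sensitivity, and any likelihood ratio built on it, inherits that balance.

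This is distinct from the effect of raised prevalence on predictive values. Recomputing those at another prevalence takes sensitivity and specificity as given, so it would leave the severity effect untouched. At stake is the early-detection statement: moderately raised pressure is where misses concentrate, and a pooled figure could make a normal app reading look more reassuring than the data justify.

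**Working it through.** The article gives no sensitivity to reproduce. Its one computed figure, power above 95%, does not bear on this point.

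**Severe share among those above 130 mm Hg (f)**
- Nested quotas: 20/40 = 0.50. This is 600 of 1200 if the base is 3000, or 420 of 840 if the base is the 70% (2100), so the share is the same on either base.
- Separate groups (40% at 130-160 plus 20% above 160): 20/60 = 0.33.
- 20% taken as a share of the hypertensive group: 0.20.

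**Assumptions (none is given in the documents except where noted)**
- Cut-off 130 mm Hg, which is the threshold Textbox 2 uses for hypertension.
- App error normal and unbiased, with SD 10, 15 or 18.8. The last follows from the systolic limit in Table 2, MAE 15: 15 × √(π/2) = 18.8.
- Natural systolic distribution N(122, 15), N(125, 16), N(128, 17) or N(132, 18) (mean, SD). The natural share of cases above 160, f₀, is then about 2% to 11%.

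**Formulas**
- Pooled sensitivity = f × Se(>160) + (1 − f) × Se(130-160), with each band's sensitivity found by integrating P(app > 130) over the band.
- Overstatement = (f − f₀) × [Se(>160) − Se(130-160)].
- LR− = (1 − Se)/Sp. With the same specificity, the ratio of LR− values is (1 − Se pooled)/(1 − Se natural).

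**Worked case: N(125, 16), error SD 15.** Band sensitivities are 0.725 and 0.989, f₀ = 0.038 and specificity is 0.788. The natural mix gives 0.735 and LR− = 0.265/0.788 = 0.34.

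| Reading | f | Pooled sensitivity | Excess over natural | LR− |
|---|---|---|---|---|
| Nested | 0.50 | 0.857 | 0.122 | 0.18 |
| Separate groups | 0.33 | 0.813 | 0.078 | 0.24 |
| 20% of hypertensives | 0.20 | 0.778 | 0.043 | 0.28 |

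**All 12 combinations of distribution and error SD**

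| Reading | Excess, percentage points | LR− relative to natural |
|---|---|---|
| Nested | 6.7 to 14.1 | 0.51 to 0.61 |
| Separate groups | 3.8 to 9.2 | 0.68 to 0.78 |
| 20% of hypertensives | 1.5 to 5.3 | 0.82 to 0.91 |

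The extremes follow from the formula. The largest gap between bands is 0.965 − 0.672 = 0.293, at N(122, 15) and SD 18.8, and (0.50 − 0.019) × 0.293 = 0.141. The smallest is 1.000 − 0.829 = 0.171, at N(132, 18) and SD 10, and (0.50 − 0.110) × 0.171 = 0.067.

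**If more natural cases are severe.** Suppose 20% to 30% of natural cases exceed 160. On the nested reading the excess runs from (0.50 − 0.30) × 0.171 = 3.4 points to (0.50 − 0.20) × 0.293 = 8.8 points, and LR− is 0.63 to 0.76 of its natural value.

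**If the app pulls readings toward the mean.** With an assumed slope of 0.5, error SD 10 and N(125, 16), the bands give 0.59 and 0.93. The nested mix gives 0.76 against 0.61 naturally, a gap of about 16 points.

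**The case against.** The strongest reply is that the article does not plan a single pooled value. It is a condensed text with no SAP shown, and cut-offs and subgroup tables are commonly left to the SAP. The enrichment is also not an error: the limitations section says it serves to test accuracy at pathological values. Both statements are correct. What stands is conditional. The quotas are stated, and they make any unstratified figure from this cohort depend on recruitment.

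A reader might infer that such a figure would mostly reflect severe cases. It would not. On the nested reading those cases carry half the weight in sensitivity and supply 55-59% of the true positives in the 12 combinations. At least 90% of the missed cases come from the 130-160 band.

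A reader might also infer that the negative likelihood ratio would look half its real size. That is close only if the quotas are nested and few natural cases exceed 160.

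Nor is a systolic-sized effect shown for HbA1c. No calculation was made for it, and the article says that "likelihood ratios will be calculated to determine the ability of the new app to accurately measure vital signs", whereas it treats HbA1c as biochemical.

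Finally, the size rests on assumed inputs. If app error grew sharply above 160, the gap between bands, and with it the excess, would shrink. The zero-bias assumption does not by itself create the effect, as the slope check shows.

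**Conclusion.** The point holds as a conditional one about spectrum. The quotas enrich for severe systolic pressure, and sensitivity or likelihood ratios pooled over the cohort would tend to overstate detection of moderately raised pressure. Under the assumptions set out above, the excess is about 7-14 points if the quotas are nested, 4-9 if they are separate groups and 2-5 if the 20% refers to hypertensives. LR− is about 0.5-0.6, 0.7-0.8 or 0.8-0.9 of its natural value respectively. The direction is the same on all three readings, provided pressures above 160 are detected better than those at 130-160 and the quota share above 160 exceeds the natural share. The text does not settle which reading applies, so no single size should be quoted. The documents do not show that only one pooled figure will be reported, and no size is claimed for HbA1c.

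**What to change.** - **Statistical Analysis:** report sensitivity and the missed fraction separately for systolic 130-160 and above 160 mm Hg. Support statements about early detection with the lower-band result. Give a pooled sensitivity or likelihood ratio only alongside the bands, or weighted to a stated case mix and shown with a range.
- **Textbox 2:** state whether the systolic quotas are nested and what their base is.
- **HbA1c:** the same banding (5.7%-6.4% and above 6.4%) may be used if diagnostic accuracy is reported for it.

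The cost is wording only, since the bands are already used for recruitment and no added participants or measurements are needed. The headline sensitivity will probably be lower and the intervals wider. With 600 cases in a band and sensitivity 0.73, the 95% half-width is 1.96 × √(0.73 × 0.27/600) = 0.036, about ±3.6 points. With 420 cases it is about ±4.2 points.
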